## Abstract

**Background:**

Tracheal intubation is a core skill in airway management for anesthesiologists as well as for other medical professionals involved in advanced airway procedures. Traditionally, tracheal intubation in hospitals has been performed using a Macintosh blade for direct laryngoscopy (DL). However, recent literature increasingly supports the potential benefits of routine video laryngoscopy (VL). The aim of this study was to assess whether primary training in hyperangulated VL improves the first-pass success rate of tracheal intubation among first-year anesthesiology residents, compared to conventional DL training, in the operating room.

**Methods:**

The JuniorDoc-VL Trial is a randomized, controlled, patient-blinded clinical trial of novice anesthesiology residents trained in DL and VL. Thirty residents will be randomly assigned to either the intervention group (VL group) or the control group (DL group) with a 1:1 allocation. The first-pass-success (FPS) rates (primary endpoint) and complication rates (secondary endpoint) will be compared between groups.

**Discussion:**

We hypothesize that the primary use of hyperangulated video laryngoscopy (VL) in the experimental group will increase first-pass-success rates among inexperienced residents and reduce complication rates associated with advanced airway management in a mixed patient population. This study may provide an opportunity to develop strategies that allow physicians not routinely involved in anesthesia to effectively learn and maintain their skills in tracheal intubation.

**Trial registration:**

ClinicalTrials.gov Registry (NCT06360328). Registered on 09.04.2024.

## Administrative information

Note: the numbers in curly brackets in this protocol refer to SPIRIT checklist item numbers. The order of the items has been modified to group similar items.

## Introduction

### Background and rationale {6a}

Traditionally, elective tracheal intubation in hospital settings is performed using a Macintosh blade for direct laryngoscopy (DL). However, visualizing the glottis and vocal cords with DL can be challenging, particularly in patients with difficult airway anatomy. The success rate of DL is highly dependent on the physician’s level of training and expertise, highlighting the importance of skill acquisition and experience in airway management [1]. Like all manual techniques and skills, endotracheal intubation (ETI) is subject to a learning curve [2]. This prompts the question of how many ETI procedures are required to achieve sufficient proficiency and reliably estimate the likelihood of success for this invasive procedure. According to the literature, first-pass success (FPS) rates for tracheal intubation using conventional direct laryngoscopy range between 50 and 87%, highlighting the variability in outcomes depending on skill level and patient factors [3–5]. In recent years, VL have become increasingly established in clinical practice. Like all medical devices, VL systems have both advantages and limitations. While VL can enhance airway visualization and potentially improve intubation success rates, it may also be associated with prolonged or unsuccessful intubation attempts in certain scenarios [6–8]. Nevertheless, growing evidence suggests that an increasing number of intubation attempts is associated with a higher risk of complications. Multiple intubation attempts can lead to serious respiratory and hemodynamic issues, including hypoxemia, regurgitation, aspiration, airway trauma, and in extreme cases, cardiac arrest [9–11]. Therefore, international guidelines on airway management emphasize the importance of limiting the number of tracheal intubation attempts [12, 13]. First-pass tracheal intubation success is a valid outcome because it demonstrates objectivity and a relationship with patient morbidity and mortality [14].

However, there is considerable heterogeneity across studies conducted in the operating room regarding the first-pass tracheal intubation success rates when using VL [13]. In recent years, VL has become widely available in both hospital and prehospital settings. Despite its widespread use, it remains unclear whether the routine application of VL reduces the incidence of failed tracheal intubations [15]. Another unresolved issue in the literature is the selection of the appropriate blade for VL. The various blade shapes offered by different manufacturers vary in size and curvature, which may influence intubation outcomes. With the increasing use of VL, numerous studies have been published comparing its effectiveness with that of DL [4, 15]. There is a wide range of devices marketed as video laryngoscopes, each with significant differences in design and application. These variations in device characteristics may lead to discrepancies in performance outcomes [16]. As a result, it is nearly impossible to generalize the findings of these studies to all VL devices, VL blades, and clinical settings. A major limitation in some comparative studies is that intubations were performed exclusively by experienced practitioners, which does not accurately reflect clinical reality [17]. It remains unclear how success rates in acquiring the skill of tracheal intubation differ between conventional direct laryngoscopy (DL) and hyperangulated video laryngoscopy (VL). While previous studies provide evidence for the learning curve associated with conventional DL, no direct head-to-head comparison has been made between these two laryngoscopy techniques [1].

We hypothesize that the acquisition of video laryngoscopy skills using a hyperangulated blade for routine tracheal intubation will lead to a higher first-pass success rate compared to conventional direct laryngoscopy among inexperienced first-year anesthesiology residents in the operating room.

### Objectives {7}

The aim of this study was to investigate whether primary training in hyperangulated VL among first-year anesthesiology residents improves the success rate of first-pass tracheal intubation compared to direct laryngoscopy training in the operating room.

### Trial design {8}

The JuniorDoc-VL study is a randomized, controlled, patient-blinded trial of novice anesthesiology residents (< 1 month) trained in conventional DL and VL. The study design is illustrated in Fig. 1. The participating residents (*n* = 30) are randomly assigned 1:1 to either the DL group (control group) or the VL group (intervention group). Residents are allocated to one of the two groups once at the start of their clinical work in anesthesiology. This signifies that the overall study can be evaluated on the basis of 6.000 ETIs, which represents a significant sample size. The principal aim of this trial is to demonstrate that the experimental treatment (VL) is superior to the control (DL).

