#### Intervention group

From the first week of clinical activity, the intervention group performs video laryngoscopy with a hyperangulated blade as the standard method for every ETI. They are supervised by a board-certified anesthetist during each induction of general anesthesia. Following the completion of 200 ETI procedures by each resident within their randomized group (VL), the evaluation was concluded. For each ETI, residents indicated whether the following difficulties were present. Furthermore, the residents were asked to indicate whether any of the following complications had occurred in the case of each ETI. In addition, the rate of complications in both groups will be monitored by the study team.

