### Sample size {14}

The calculation of the sample size was based on achieving successful tracheal intubation on the first attempt and on organizational aspects and realistic feasibility. In recent trials, the VL demonstrated a first-attempt success rate of 92–97% in a mixed resident population. The study’s power was determined by assuming an 80% first-pass success rate in the DL group [1] and 92–94% in the VL group [16, 18]. This study was chosen for the sample size calculation because the aim was to compare VL and DL in first-year anesthesia residents in the operating room. Based on the current first-pass success rate, we hypothesized that a 10% increase in the VL group compared to the DL group would constitute a significant improvement in advanced airway management. To detect a difference in means of 10, with sample sizes of 15 in Group 1 (VL) and 15 in Group 2 (DL), the power is 0.66262. The power was computed using PASS 2024, version 24.0.2 NCSS, LLC. Kaysville, UT, USA.

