## Assignment of interventions: allocation

### Sequence generation {16a}

At the beginning of the study, each resident is randomly assigned to either the intervention group (VL group) or the control group (DL group) in a 1:1 allocation. Each resident then performs all tracheal intubations within their assigned group. This approach ensures that the decision to randomize is made only at the outset of the study, with no switching between groups thereafter. This implies that each participant is immediately aware of their assigned study group following the enrolment phase and throughout the entirety of the study. The study employs Randomizer AT, a randomization software developed by the Medical University of Graz Institute for Medical Informatics, Statistics, and Documentation (IMI). Therefore, factors such as gender distribution cannot be influenced.

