## Statistical methods

### Statistical methods for primary and secondary outcomes {20a}

A parallel two-group design will be used to test whether the Group 1 mean is different from the Group 2 mean (H0: μ1 − μ2 = 0 versus H1: μ1 − μ2 ≠ 0). The comparison will be made using a two-sided, two-sample equal-variance t-test, with a Type I error rate (α) of 0.05. The common standard deviation for both groups is assumed to be 10. The distribution of the data of the primary endpoint (FPS) is tested for normality using the Shapiro-Wilk test. In addition, graphical methods such as histograms and Q-Q plots are used to visually assess the distribution of the data. To compare FPS values between groups, either the parametric t-test (for normally distributed data) or the non-parametric Mann-Whitney U-test (for non-normally distributed data) is used, depending on the distribution. The choice of test was made based on the results of the normality test. Multiple logistic regression analysis of subgroup factors will allow us to assess the factors affecting FPS when comparing DL with VL, such as age, sex, ASA, BMI and provider experience. Cox regression can be used to evaluate the combined impact of the method and other explanatory variables. We used the following software for the calculation PASS 2024 Power Analysis and Sample Size Software (2024). NCSS, LLC. Kaysville, Utah, USA.

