### Analysis of the secondary outcomes

Complications will be analyzed with Kaplan-Meier curves and the log-rank test. The comparison of the view of the glottis will be analyzed using the Wilcoxon rank-sum test. Logistic regression and Cox regression will be used to explore the effect of additional explanatory variables.

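### The design section names 6,000 intubations as the basis of evaluation, and the intubation-level analyses make no stated allowance for 200 intubations per resident; the primary test on 15 v 15 residents is not affected

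*Protocol article*

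**What the plan says.** The unit of randomisation is clear. The abstract says: "Thirty residents will be randomly assigned to either the intervention group (VL group) or the control group (DL group) with a 1:1 allocation". Under Sequence generation {16a}: "Each resident then performs all tracheal intubations within their assigned group". For the VL arm, Intervention group says: "Following the completion of 200 ETI procedures by each resident within their randomized group (VL), the evaluation was concluded"; Control group sets the same number for DL. Sample size {14} works with residents: "To detect a difference in means of 10, with sample sizes of 15 in Group 1 (VL) and 15 in Group 2 (DL"), and it reports that "the power is 0.66262".

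Trial design {8} gives a different basis: "This signifies that the overall study can be evaluated on the basis of 6.000 ETIs, which represents a significant sample size". The figure is six thousand, that is 30 × 200.

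Statistical methods {20a} gives the primary comparison of mean FPS by t-test or Mann-Whitney test and then adds: "Multiple logistic regression analysis of subgroup factors will allow us to assess the factors affecting FPS when comparing DL with VL". The listed factors include age, sex, ASA class and BMI, which belong to the patient, so each row of that model is an intubation. Analysis of the secondary outcomes plans Kaplan-Meier curves and a log-rank test for complications and a rank-sum test for glottic view, and continues: "Logistic regression and Cox regression will be used to explore the effect of additional explanatory variables". No random effect, GEE, robust variance or resident-level summary is named in either section.

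**The concern.** All 200 intubations by one resident share that resident's skill and that resident's arm. A comparison of arms therefore draws its information from 30 residents, however many intubations each performs. The sentence in Trial design {8} tells the analyst otherwise, and the methods sections give nothing to counter it.

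Two results are at stake. The ETI-level model of FPS contrasts the devices on the primary outcome. Complications are the secondary endpoint named in the abstract and part of the trial's hypothesis. With a stated primary power of only about 0.66, an inconclusive primary test beside an ETI-level model with a far smaller p-value is a realistic outcome. Readers would need to know that the second p-value is not trustworthy.

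**Working it through.** **Inputs from the protocol**
- 30 residents, 15 per arm (Abstract; Sample size {14}).
- 200 ETIs per resident (Intervention group; Control group), so 3,000 per arm.
- FPS of 80% with DL; difference in means 10 (Sample size {14}).
- Common SD 10, two-sided alpha 0.05 (Statistical methods {20a}).

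**Assumptions**
- The SD of 10 is the spread, in percentage points, of residents' observed FPS over their 200 ETIs. This is inferred from the use of means, an SD and 15 per group.
- SDs of 5 and 4 points are added to show the range. They are not in the document.

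**1. The plan's own power figure.** For a two-sample t-test with 28 degrees of freedom, the noncentrality is 10 / (10 × √(2/15)) = 2.74 and power is 0.753, not 0.66262. The stated value comes out exactly with a difference of 9. That mismatch is a separate matter. What counts here is that the figure belongs to 15 v 15 residents: with 3,000 independent ETIs per arm, power for 80% v 90% would be essentially 1.00.

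**2. Design effect for FPS.**
- Variance of a resident's FPS if ETIs were independent: p(1 − p)/200 = 0.8 × 0.2 / 200 = 0.0008.
- Variance assumed by the plan: 0.10² = 0.01.
- Design effect: 0.01 / 0.0008 = 12.5.
- ICC: (12.5 − 1)/199 = 0.058.
- Effective number of ETIs: 6,000 / 12.5 = 480.

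**3. True type I error of an unclustered arm comparison at nominal 5%.** The formula is 2 × [1 − Φ(1.96/√DEFF)].

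| SD between residents (points) | Design effect | Effective ETIs | Type I error |
|---|---|---|---|
| 10 (plan) | 12.5 | 480 | 0.58 |
| 5 (assumed) | 0.0025/0.0008 = 3.1 | 1,920 | 0.27 |
| 4 (assumed) | 0.0016/0.0008 = 2.0 | 3,000 | 0.17 |

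**4. Check by simulation.** Beta-binomial data with no arm difference, SD 10 points, 15 v 15 residents and 200 ETIs each (20,000 runs) gave these rejection rates:

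| FPS | Unclustered log odds ratio test | Resident-level t-test |
|---|---|---|
| 80% | 0.59 | 0.049 |
| 85% | 0.62 | 0.048 |
| 90% | 0.68 | 0.045 |

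**5. Precision.** The resident-level standard error of the difference is 10 × √(2/15) = 3.65 points. Treating ETIs as independent at 80% v 90% gives 100 × √((0.16 + 0.09)/3000) = 0.91 points, smaller by a factor of 4.

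**6. Limits.** Steps 2 to 5 concern an unadjusted arm contrast in FPS. Covariates would reduce the inflation only as far as they explain the differences between residents. The document gives no between-resident spread for complications or glottic view, so no figure can be given for them. The design effect does not carry over to factors such as age or BMI that vary among one resident's patients.

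**The case against.** The strongest reply is that the inference that matters is sound. The power calculation and the primary test rest on 15 v 15 residents, and the 6,000 figure enters neither. This stands. A reader of the sentence in Trial design {8} might infer that the plan overlooks the 30 residents throughout, or that the Mann-Whitney test for FPS runs on 6,000 rows. The sample size and primary analysis sections do not support either reading.

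A second reply is that the protocol nowhere says ETIs are treated as independent, and that a condensed article may leave random effects or robust variances to the analysis plan. Independence is indeed an inference. The reply would suffice if the article were merely silent, but Trial design {8} states affirmatively that the 6,000 ETIs are a basis of evaluation. An analysis plan that handled clustering properly would have to depart from that sentence.

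Third, the scope of some analyses is uncertain. The secondary outcome list ties glottic grading to the use of VL, so the rank-sum test may not compare arms. No time axis is given for the log-rank and Cox analyses; one event time per resident would not raise the problem. The logistic model is also described as exploring factors. These points stand as limits, and the finding covers those analyses only where they compare arms across intubations.

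**Conclusion.** The point holds in a limited form. The sentence in Trial design {8} is wrong as written: 6,000 ETIs are not the sample size for comparing the arms. The ETI-level analyses are specified without any allowance for resident. If they are run on independent rows, their arm contrasts will be anticonservative.

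For FPS, type I error is about 58% at nominal 5% if the plan's SD of 10 points at 80% is the spread of resident-level FPS. It is about 27% and 17% at assumed SDs of 5 and 4 points, so the conclusion does not depend on the plan's SD being right.

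It would be tempting to apply the 58% to every secondary p-value. The documents do not support that: the figure belongs to the unclustered FPS arm contrast alone. For complications and glottic view the size of the inflation is unknown.

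**What to change.** 1. In Trial design {8}, replace the sentence with wording such as: *The sample size is 30 residents; the 6,000 ETIs are repeated observations within residents.*
2. For every ETI-level comparison of arms, name one of: a model with a random intercept for resident; GEE or robust variance clustered on resident; or a comparison of resident-level summaries. The first two need a small-sample correction for 30 clusters. Time-to-event analyses across ETIs need clustered or frailty versions.
3. Keep a non-identifying resident code in the analysis file. Data management {19} and Confidentiality {27} provide for anonymisation once the 200 ETIs are complete and do not say whether such a code survives. Without it, clustering cannot be modelled afterwards. Recruitment opened in April 2024 and a resident's series is expected to take about a year, so this should be settled first.

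The cost is a change of wording, the retained code, and wider confidence intervals for arm comparisons. The primary analysis is unchanged.

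A term for ETI sequence number by arm could be added to the FPS model to describe the learning curve. That is optional and separate, and it depends on ETI order being recorded, which the document does not state.

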**Fig. 1 Fig1:**
[figure not shown]
The study design

## Methods: participants, interventions, and outcomes

### Study setting {9}

The study is a single-center randomized, controlled trail, which takes place at the University of Heidelberg, Medical Faculty Heidelberg, Department of Anesthesiology, Germany. Our hospital is a university maximum care hospital with 2599 beds. The Department of Anesthesiology provides comprehensive anesthesiologic services and oversees the intensive care units, offering a full range of intensive care therapies, including extracorporeal procedures. All specialist medical departments are represented within the university hospital.

### Eligibility criteria {10}

#### Inclusion criteria

All new (less than 1 month) residents of the University Hospital Heidelberg, Department of Anesthesiology who wish to participate voluntarily in the study.

#### Exclusion criteria

Rejection of study participation by the residents.

### Who will take informed consent? {26a}

The residents are duly informed and consent is obtained. In accordance with German legislation, this procedure may only be performed by a physician from the study team.

### Additional consent provisions for collection and use of participant data and biological specimens {26b}

No biological samples are included in this study.

## Interventions

### Explanation for the choice of comparators {6b}

The use of video laryngoscopy for elective anesthesia in the operating theatre is a controversial topic in the literature due to the advantages and disadvantages of each method of advanced airway management [6, 8]. It is important to know the learning curves for different methods of airway management in order to be able to define the teaching but also the recommendations for certain standard numbers of procedures. In order to ascertain whether the success rates and learning curves for the two groups are disparate, it is necessary to conduct a randomized study and undertake a direct head-to-head comparison.

### Intervention description {11a}

After providing informed consent, residents are given an evaluation form to independently document endotracheal intubation (ETI) procedures they have previously performed during their internship or medical school training. This process enables us to assess the extent of each resident's prior experience with advanced airway management. In this study, the intervention group will utilize video laryngoscopy as the standard method for airway management, specifically employing the hyperangulated D-Blade® (C-MAC®, Karl Storz, Germany) for all elective intubations [6, 8]. To ensure the inclusion of a patient population representative of real-world clinical scenarios (real-world data), the study incorporates both patients with no anticipated risk of difficult tracheal intubation and those with an expected difficult airway.

All patients are monitored for electrocardiography (ECG), oxygen saturation (SpO_2_), and arterial blood pressure (non-invasively or invasively, as appropriate). In the VL group, a malleable style was utilized for tracheal tube placement. This approach is consistent with the clinical standard. Preoxygenation is achieved using the device selected by the provider based on patient characteristics and the clinical standard operating procedure (EtO2 > 80%).

Residents record the number of attempts and the techniques employed for tracheal intubation on the case report form (CRF) immediately following the airway management procedure. Each intubation was supervised by an experienced board-certified consultant anesthesiologist, ensuring adherence to safety standards and providing immediate guidance when necessary. An attempt to secure the airway was defined as the insertion of the laryngoscope blade into the mouth, details are shown in Table 1. In accordance with the internal hospital protocol, residents are required to consult an anesthesiologist specialist following two unsuccessful attempts. In accordance with this protocol, the participants in the present study will be replaced by the consultant or instructed by him following two unsuccessful attempts. In the event of any safety-critical situations arising (e.g., desaturation, severe hypotension, airway injuries, or if the consultant deems it necessary), the intubation by the resident will be aborted. The number of subsequent attempts made by this clinician to successfully secure the airway was also recorded on the case report form (CRF). No specific training is provided prior to the use of either intubation method. In accordance with our internal standard, the participants receive a brief introduction to the medical devices and their correct use according to the manufacturer's instructions as part of the on-boarding process. This is also required by medical legislation in Germany.

**Table 1 Tab1:** Definition of the important outcome variables

First-Pass-Success	Desaturation	Hypotension
The initial tracheal intubation attempt was defined by the insertion of a laryngoscope blade and/or tracheal tube into the patient’s mouth		
The initial intubation attempt was considered to have failed if it did not result in successful endotracheal intubation, with or without an attempt to pass the tube	<90% O_2_saturation if not pre-existing and without a prescribed time period	< 65 mmHg mean arterial pressure (MAP) if not pre-existing and without a prescribed time period
Subsequent attempts at intubation were characterized by the reinsertion of an endotracheal tube or the insertion of the same or a new laryngoscope blade	So a single valid measurement <90% is documented with the term “desaturation”	

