### Outcomes {12}

Study participants will independently document various parameters on the case report form (CRF) immediately after tracheal intubation or, at the latest, shortly thereafter. Any complications arising during the procedure will be recorded no later than after extubation. This approach ensures that the documentation is provided in a timely manner and is directly related to the case.

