#### Secondary outcome measure

Complications such as oxygen desaturation below SpO_2_ 90%, regurgitation, and dental or soft tissue trauma.Number of attempts made during laryngoscopy.The level of training with intubation success.Any failures or transitions to other rescue techniques.The use of OELM techniques such as BURP, CP, or adjustment of the participant's head and neck position.When using VL, record the occurrence of fogging and assess the glottic view using the Cormack-Lehane classification and the Percentage of Glottic Opening Score.Indications of difficult airway management (e.g., Mallampati Score, limited mouth opening)

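### Desaturation and hypotension have no stated observation window around intubation, so events unrelated to laryngoscopy could enter the secondary complication comparison

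*Protocol article*

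**What the plan says.** All references are to the protocol article.

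- **Intervention description {11a}, Table 1.** Hypotension is "< 65 mmHg mean arterial pressure (MAP) if not pre-existing and without a prescribed time period". Desaturation is below 90% oxygen "saturation if not pre-existing and without a prescribed time period", and the table adds for this event: "So a single valid measurement <90% is documented". The section Definition of the important outcome variables makes Table 1 the place where the key outcomes are defined.
- **Outcomes {12}.** Most parameters are documented immediately or shortly after intubation. For complications the rule is different: "Any complications arising during the procedure will be recorded no later than after extubation".
- **Intervention group.** Residents indicate "whether any of the following complications had occurred in the case of each ETI". No start or end time is attached.
- **Secondary outcome measure.** The list reads "Complications such as oxygen desaturation below SpO_2_ 90%, regurgitation, and dental or soft tissue trauma". Desaturation is named; hypotension is not.
- **Abstract, Discussion.** The hypothesis is that VL will "reduce complication rates associated with advanced airway management". The Abstract's Methods paragraph makes complication rates the secondary endpoint. Objectives {7} mentions only first-pass success.
- **Analysis of the secondary outcomes.** "Complications will be analyzed with Kaplan-Meier curves and the log-rank test". No time origin or end of observation is given.

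**The concern.** The complication hypothesis is about events tied to airway management. A blood pressure drop from bleeding well into surgery, or a low saturation reading at emergence, will usually say nothing about the laryngoscope. If the definition admits such events, they add to the counts in both arms and pull the relative effect towards no difference.

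Dilution is not the only risk. Outcomes {12} has residents complete the forms themselves, and Sequence generation {16a} says each knows the assigned group throughout. Where the end of observation is left to the person filling in the form, residents may differ in how late they keep recording, and that could differ by arm.

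The between-arm monitoring of adverse events promised in Adverse event reporting and harms {22} would be open to the same problem if it draws on these records. Unless the form carries a time for each event, early and late events cannot be separated afterwards.

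**Working it through.** **Step 1: does the text fix a window?** The article states no complication rate, effect size or power for the secondary outcomes, so there is no figure to reproduce. The check starts with the wording.

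- The remark in Table 1 about a time period most naturally means that no minimum duration is required, because the table goes on to say that one valid reading is enough. The remark alone does not show that a window is missing.
- The limit in Outcomes {12} is a deadline for filling in the form. The qualifying condition is that the event arises during the procedure.
- The article uses *procedure* in two senses. Intervention description {11a} and Intervention group apply it to intubation; Subgroups applies it to the operation (general or bariatric surgery).
- No other section gives a start, an end or an attribution rule.

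The window is therefore open to two readings. One confines events to the intubation; the other covers the whole case.

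**Step 2: what the wider reading could do if background events are equal in both arms.** All rates here are assumptions. Let p be the airway-related risk and b the risk of an unrelated event, independent of p and equal in both arms. Then:

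observed risk = 1 − (1 − p)(1 − b)

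Example with p = 10% (DL) and 6% (VL), b = 10%: 1 − 0.90 × 0.90 = 0.190 and 1 − 0.94 × 0.90 = 0.154; risk ratio VL/DL = 0.154/0.190 = 0.81.

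For power, the article gives 30 residents × 200 intubations = 6000, or 3000 per arm. The effective number per arm is n = 3000/(1 + 199 × ICC), with an assumed ICC (correlation of outcomes within a resident) of 0, 0.01 or 0.02. Two-sided alpha of 0.05 is borrowed from the primary test. With p̄ the mean of the two observed risks:

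power = Φ{ [ |p_DL − p_VL| − 1.96√(2p̄(1 − p̄)/n) ] / √[ (p_DL(1 − p_DL) + p_VL(1 − p_VL))/n ] }

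| Airway-related risk, DL v VL | b | Observed risk, DL v VL | Risk ratio | Power at ICC 0 / 0.01 / 0.02 |
|---|---|---|---|---|
| 10% v 6% | 0 | 10.0% v 6.0% | 0.60 | >0.99 / 0.91 / 0.73 |
| 10% v 6% | 10% | 19.0% v 15.4% | 0.81 | 0.96 / 0.57 / 0.38 |
| 10% v 6% | 30% | 37.0% v 34.2% | 0.92 | 0.62 / 0.26 / 0.17 |
| 6% v 3% | 0 | 6.0% v 3.0% | 0.50 | >0.99 / 0.90 / 0.71 |
| 6% v 3% | 10% | 15.4% v 12.7% | 0.82 | 0.85 / 0.41 / 0.27 |
| 6% v 3% | 30% | 34.2% v 32.1% | 0.94 | 0.41 / 0.17 / 0.12 |

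The protocol plans a log-rank test, not a comparison of proportions, so the power column shows only the direction and rough pattern of the loss.

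**Step 3: what it could do if late events are recorded unequally.** Take no true device effect, p = 6% in both arms, with late events recorded in 10% of DL cases and 5% of VL cases. Observed risks are 1 − 0.94 × 0.90 = 15.4% and 1 − 0.94 × 0.95 = 10.7%, so the risk ratio is 0.107/0.154 = 0.69 instead of 1. With the recording pattern reversed it is 0.154/0.107 = 1.44. The bias can favour either arm.

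**The case against.** Several points on the other side are sound.

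- **The wording does not say that unrelated events count.** A reader might infer from Table 1 and the extubation deadline that every low reading up to extubation is an outcome event. The documents do not support that. The time-period remark concerns duration, the deadline concerns paperwork, and complications are asked for per intubation. Intervention description {11a} also lists desaturation and severe hypotension among the reasons for aborting the resident's attempt, which is a peri-intubation setting. What stands is that the wider reading is possible and nothing rules it out.
- **Hypotension may not be in the comparison at all.** It is defined in Table 1 but absent from the secondary outcome list, whose wording is open-ended. The point therefore rests first on desaturation, which is named.
- **Late events can be airway-related.** Background and rationale {6a} names regurgitation and aspiration among the consequences of repeated attempts, and later desaturation could follow from these. It would be too strong to say that no late event can depend on the device.
- **The article is condensed and the case report form is not shown.** The form may carry times. But the article prints the operative definition of these outcomes, and that definition has no window, so this is more than omitted detail.
- **The rates are assumed.** This is correct; the table in the working shows direction, not size.

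**Conclusion.** The concern holds in a limited form. Table 1 and Outcomes {12} fix no observation window for desaturation or hypotension, and an ambiguous word leaves it to the resident whether the intubation or the whole case is meant. Events unrelated to laryngoscopy could be counted. Under equal background rates this dilutes the comparison; under unequal recording by unblinded residents it could bias it either way.

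The size cannot be derived from the document. The risk ratios of 0.81 to 0.94 rest on assumed airway-related risks, assumed background risks of 10% and 30%, independence of the two kinds of event and equal background in both arms.

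Two stronger readings are tempting. One is that a null result on complications would be uninterpretable. The documents do not support this: how many unrelated events would be recorded is unknown, and even at 30% background the illustrated difference shrinks from 4.0 to 2.8 points (37.0% − 34.2%) and does not vanish. The other is that a stated trial objective is compromised. Complications are a secondary endpoint and a hypothesis; Objectives {7} covers first-pass success only, and the primary outcome is untouched. This is a worthwhile, inexpensive improvement to a secondary endpoint.

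**What to change.** 1. In Table 1 and on the case report form, count desaturation and hypotension as airway-management complications only within one pre-specified window with a stated start and end around induction and intubation, identical in both arms.
2. Keep the extubation deadline for injuries that are seen late, such as dental or soft tissue trauma.
3. If later desaturation or hypotension is of interest, record it as a separate item outside the secondary endpoint.
4. Under Secondary outcome measure, state whether hypotension belongs to the endpoint.
5. Reconcile the window with the planned Kaplan-Meier and log-rank analysis by stating the time origin and the end of observation.

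**Cost.** A line or two in Table 1 and on the form, and a protocol amendment. Fewer events will be counted, and some late desaturation that does stem from airway management may be lost; the separate item in step 3 keeps it visible. Recruitment began in April 2024 and is expected to run to the end of 2027. If forms already completed carry no event time, those records can enter only a sensitivity analysis, so an early change is worth more than a late one.
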